**Fig. 1 Fig1:**
[figure not shown]
IMPACT project stages

### STAGE 1: co-design of implementation strategies

#### Engagement of the IMPACT steering committee

A steering committee of key stakeholders with relevant research, clinical/system expertise or lived experience (researchers, patients, patient advocacy group members, physiotherapists, GPs, orthopaedic surgeon) will be recruited via word of mouth and personal communication. The main purpose of the committee is to discuss and agree on implementation strategy designs that are considered suitable to integrate GLA:D® in the existing routines of the Irish healthcare system. Three to four online meetings will take place each year to achieve this objective, along with other tasks as outlined below.

#### Co-design

The co-design and tailoring of multi-level implementation strategies will involve a series of review stages and consultations with the steering committee, using a three-step iterative process:STEP 1: Identify barriers and enablers to implementation informed by (i) implementation theory, (ii) research evidence, (iii) local context, and (iv) expert consensus.(i)Implementation Theory

The steering committee members will vote on barriers that are deemed relevant to the project using a list of theory-driven CFIR constructs (*n* = 39) by each domain [33]. These barriers will subsequently be used with the CFIR- Expert Recommendations for Implementing Change (ERIC) Barrier Busting Query Tool [35] to match with an appropriate enabler or strategy. This tool was developed by Powell et al. using a Delphi process to generate expert consensus on commonly used or effective strategies [35] and will form the initial list of barriers and enablers to implementation. To further operationalise the CFIR domain “characteristics of individuals”, this domain will be split into two, namely: “characteristics of physiotherapists” and “characteristics of patients” to address the different barriers and strategies that will be applied to each.(ii)Research Evidence

Previous published reviews on barriers and enablers to implementation of exercise and education for osteoarthritis will be reviewed and mapped to CFIR constructs [21–23, 36, 37]. A scoping review of strategies used for the implementation of exercise programmes for chronic conditions in healthcare and community settings will be carried out. The purpose of this review is to understand the type and evaluation of existing implementation strategies used globally. Identified elements from this review will be mapped to CFIR construct headings where relevant.(iii)Local Context

Due to the disparity between recommended exercise guidelines for OA and patient referral or access to appropriate exercise programmes, there is a need to understand the local beliefs, barriers and enablers to inform development of the implementation strategies. This will be carried out via three cross-sectional online self-administered surveys for physiotherapists, GPs and patients with OA in Ireland respectively. Three tailored online cross-sectional surveys (designed using Qualtrics®), adapted from the work of Cottrell et al. [38], Holden et al. [39] and Davis et al. [40], will be reviewed for face validity by members of the steering committee prior to distribution. All surveys will be advertised via social media (Twitter, LinkedIn) and word of mouth. In addition, the GP survey will be distributed to the Irish College of General Practitioners network, the physiotherapist survey will be distributed to the Irish Society of Chartered Physiotherapists network and the survey for people with OA will be advertised in various newsletters, community noticeboards and Arthritis Ireland social media. Exercise beliefs statements will be rated on a 5-point Likert scale from strongly agree to strongly disagree and collapsed to a binary scale (agree vs. disagree/neither) and multiple choice and open questions will be given for identification of barriers and enablers. Results of each survey will be analysed with assistance from the online CFIR codebook template to identify barriers and enablers under appropriate construct headings.(iv)Expert/Steering Committee Consensus

Other barriers, enablers and strategies identified by steering committee members or in consultation with other relevant clinical, patient and policy stakeholder groups (e.g. Irish College of General Practitioners, National Clinical Programme for Trauma and Orthopaedic Surgery (orthopaedic consultants), Arthritis Ireland (patient and carer advocacy group), Irish Society for Chartered Physiotherapists etc.) will be sought, discussed and considered as relevant.STEP 2: Combine findings from (i) to (iv) in STEP 1 under each CFIR construct, to create or tailor distinct and actionable implementation strategies. The ERIC Barrier Busting Query Tool will be applied again to query any newly identified barriers. Strategies will be grouped according to targets as appropriate (e.g. patient engagement, healthcare professional engagement and training, changing policy, community partnerships). Each strategy will be mapped to the relevant CFIR construct barrier(s) and will include a method to evaluate the impact of each strategy. Reporting guidelines for implementation strategies as recommended by Proctor et al. will be used where appropriate [24]. An example is provided in Table 1.STEP 3: The steering committee will review each strategy and discuss relevant changes or additions. Information presented in the GLA:D® education materials will also be adapted to suit the Irish context and health system for items related to e.g. terminology, models of care and medications as relevant in this step.

**Table 1 Tab1:** Example of reporting methods for implementation strategies using prerequisites suggested by Proctor et al. [24]

Implementing GLA:D in clinical practice (Name it)	
Strategy (Define it)	Specify it
1. Each PT will need to work with the clinic manager and colleagues to have dedicated time to implement. A GLA:D Ireland PT Toolkit to assist with these conversations will detail: i. Programme evidence, ii. Programme requirements in terms of time, space, equipment and process mapping, iii. Alignment with government or international policy and waiting list support, iv. Opportunities to be involved in research or improve service with data or benchmark patient or clinic outcomes.	**Actor:** Researchers, lead implementer and clinic managers/colleagues
	**Action:** Researchers produce toolkit and encourage discussion. Lead implementers initiate discussion in clinic and present case.
	**Target:** Meso-level. Number of sites trained and implementing the programme. Nature of feedback from implementers in qualitative interviews.
	**Temporality:** Toolkit presented at training course. Discussion initiated immediately following training. Re-visited as needed.
	**Dose**: Once at initiation of implementation. Re-visited as needed.
	**Implementation outcome affected:** acceptability, adoption, appropriateness
	**Justification (CFIR barrier addressed):** Availability of resources (inner setting), Relative advantage (intervention characteristics) **(References in literature):** Briggs et al. 2019, Lau et al. 2016

### STAGE 2: pilot and evaluate the implementation strategies

This stage will involve piloting the implementation strategies co-designed in stage one and evaluating the effectiveness of the strategies.

#### Training of physiotherapists

An initial convenience sample of engaged physiotherapists will be contacted via word of mouth through co-investigators and steering committee members to take part in the first GLA:D® training course and pilot study. This sample will be representative of different regions and across private (small and large clinic) and public (primary care and orthopaedic hospital) healthcare settings in Ireland. These physiotherapists will participate in a 2-day continuous professional development course giving them the requisite skills to diagnose OA and deliver care as described in the clinical guidelines. The course theory summaries latest evidence on treatment of OA, as well as practical instructions in the specific protocol of GLA:D®, including delivering patient education, supervising and instructing neuromuscular exercise and the use of the online registry [15]. The course will initially be delivered by representatives from GLA:D® Denmark, with additional training on relevant implementation strategies identified in stage one provided by [name]. A patient representative will also be present at the training to provide appropriate input. This will give the physiotherapists access to an implementation ‘toolkit’ and online platform with all the material needed to deliver GLA:D® locally in the clinic.

#### GLA:D® pilot programme delivery

GLA:D-trained physiotherapists (*n* = 8–10) will make use of existing or new referral sources to invite people with hip or knee OA to take part in the GLA:D® programme, as applicable for each setting. These sources include but are not restricted to clinic or orthopaedic waitlist, GP or other healthcare professional referral and self-referral. Eligible participants will have ‘joint problems from knee and/or hip that have resulted in contact with the health care system’. Exclusion criteria include non-OA cause of symptoms, e.g., tumour; inflammatory joint disease, or sequelae after hip fracture; other symptoms that are more pronounced than the OA problems, e.g., chronic, generalised pain, or fibromyalgia, acute knee trauma in the past 6 months or inability to understand the English language. The GLA:D® programme will comprise two to three education sessions and 12 (twice weekly) group neuromuscular exercise sessions as described in detail previously [15]. All group sessions will be supervised by a physiotherapist and can be delivered in a face-to-face or online format, as per clinician/patient preference and capability. Participants are encouraged to continue being physically active and to exercise, either with their physiotherapist or in their local community, to sustain the effects from the treatment in the long term.

#### Evaluation of GLA:D® implementation

As established by Proctor and colleagues [41], a core set of implementation outcomes including: acceptability, adoption, appropriateness, cost, feasibility, fidelity, penetration and sustainability will be evaluated as outlined in Table 2*.* Implementation outcomes will be analysed descriptively using frequencies/proportions for categorical variables and means and standard deviations or medians and interquartile ranges for continuous variables.

**Table 2 Tab2:** Implementation outcomes and proposed method of collection

Outcome	Definition	Method of Collection (Level of analysis)
Acceptability	Satisfaction with various aspects of the programme	Survey on beliefs (Providers and patients); Survey on satisfaction at 3 months and 12 months post-programme (Providers and patients) Interview with providers: “Were you satisfied with the programme?” Interview with patients: “Were you satisfied with the programme?”
Adoption	Uptake and utilisation of the programme	Registry: Recording the number of referral sources, sites trained vs. sites implementing, trained physiotherapists and participant registrations from private and primary care settings (Providers and patients)
Appropriateness	Perceived fit, relevance, or compatibility of the programme for a given setting, provider, or consumer; and/or to address a particular issue or problem	Survey on beliefs (Providers and patients); Survey on satisfaction at 3 months post-programme (Providers and patients) Interview with providers: “How compatible is the GLA:D programme in your setting?” Interview with providers and patients: “Does the programme address a particular issue or problem?”
Cost	The financial impact of the implementation	Survey on barriers from WP1 (Providers and patients), Health utilisation and sick leave/medication use survey at 3 months and 12 months post-programme (Patients) Cost-effectiveness analysis Interview with providers and patients: “Have there been any cost implications?”
Feasibility	The extent to which the programme can be successfully used or carried out within a given setting	Collected with a survey at training course with strategies to overcome specific feasibility barriers discussed (Providers)
Fidelity	The degree to which the programme is implemented as it was prescribed in the original protocol	Interview with providers: “Did you make specific changes to the original programme? What did you change?”
Penetration	The integration of a practice within a service setting and its subsystems	Registry: recording the number screened during the study period and reporting of the absolute number and proportion of those who participated in the program as well as the number of referral sources (Providers);
Sustainability	The extent to which the implemented programme is maintained	Number of sites still running the programme at 12 months and by the end of the project (Providers); Physical activity and exercise participation at 3 and 12 months (Patients) Interview with providers: “Do you intend to continue delivering the programme?” Interview with patients: “Do you intend to continue doing the exercises?”

Semi-structured interviews will be conducted with 8–10 physiotherapists across healthcare settings (primary care, orthopaedic hospital, private practice) that have implemented the pilot programme within a five-month time-frame and those who have not implemented the programme, if appropriate. Semi-structured interviews will also be conducted with 12–15 patient participants across each setting. For people with OA, criterion purposive sampling will be used, seeking a representative sample based on sex, affected joint, disability level, duration of symptoms and number of attended sessions. The purpose of these interviews is to capture barriers and enablers to GLA:D® programme delivery and provide context related to implementation outcomes. The interview guide was adapted from Davis et al.’s [17] evaluation of GLA:D® in Canada and is presented in Additional file 4. Included topics relate to experiences providing or taking part in the programme and format (online or face-to face, if applicable), barriers or enablers encountered and any prior information or support that would have helped in delivering, taking part or adhering to the programme. Interviews will be recorded and transcribed verbatim. Interview data will be analysed thematically using a deductive approach primarily, with assistance from the CFIR codebook template for qualitative data [42, 43]. After multiple readings by the research team, codes will be assigned from units of the text and grouped into pre-defined themes using NVivo software (QSR International). Any additional themes identified using an inductive approached will be labelled as appropriate. Using reflexivity, the interviewer will also document pre-existing ideas and perspectives in an attempt to identify any biases [44]. A summary of findings from the interviews and identified themes will be presented to the steering committee to allow for additional interpretation and discussion.

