#### Evaluation of effectiveness

An electronic GLA:D® Ireland registry will collect participant consent and all therapist- and patient-reported data from baseline, 3- and 12-months follow-up. The secure REDCap™ software platform will be used to build, collect and manage all data related to the registry and research project. An evaluation of programme effectiveness relating to self-reported and measured outcomes such as pain, joint symptoms, quality of life and functional capacity (outcomes collected presented in Additional file 5) will be performed at each annual review. Effectiveness outcomes, using a pre-post design, will be analysed to evaluate change scores (baseline to 3- or 12-month follow-up) with 95% confidence intervals to determine significance (α = 0.05) and clinical significance where a published value exists. If appropriate, a mixed-effects model will be used with patient as a random effect and time as a fixed effect. Sensitivity analyses will be conducted to determine differences in results related to site of pain (knee/hip), history of joint replacement and private or public setting. IBM SPSS® Statistics 26 will be used to perform all statistical analyses.

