#### Evaluation of cost-effectiveness

A cost utility analysis will be conducted after 2 years of implementation to determine the financial impact of implementing the programme. The direct and indirect costs of implementing GLA:D® will be compared to its benefits. Using the 5-dimension EuroQol (EQ-5D) to measure health related QALYs, the raw and adjusted incremental cost-effectiveness ratio (ICER) will be calculated 1 year after the intervention. An exploration of healthcare utilisation pre- and post- participation in the GLA:D® programme will be conducted at each time-point (Additional file 3) and compared to national data from the TILDA study [45].

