Implementation strategies are further operationalised by level i.e. micro, meso, macro. It is acknowledged that certain barriers may be non-modifiable within the scope and lifetime of this research study, particularly at a macro level. Nonetheless, strategies related to policy and engagement of stakeholders will work towards tailoring messages and driving change at these levels where appropriate. It is envisaged that patient outcomes and cost effectiveness data collected after 1 year of implementation will be used to leverage and advocate to Department of Health, the Health Service Executive and other relevant bodies to fund supervised exercise and education interventions for chronic musculoskeletal conditions. It will be important to apply this data alongside international evidence to help improve models of care and pathways for people with chronic hip and knee pain.

While local context is important to include with implementation efforts, this research has relevance beyond the specific setting in which it is being conducted. As with all intervention research, implementation strategies need to be fully and precisely described, in detail sufficient to enable measurement and ‘reproducibility’ of their components [24]. The details of the participatory health research process will be reported so that implementation projects work in other care settings, for other chronic conditions and other countries can be informed by lessons learned during that process. The use of theory in this study will also enhance the scope to accumulate knowledge about overcoming barriers to implementation [34]. Therefore, the strategies deemed to be effective will be published and shared widely for potential transfer and implementation in other healthcare settings, contexts and conditions.

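### The cost schedule needs reconciling: Table 2's Cost row omits baseline, the follow-up clock has no single origin, the 1-year and 2-year cost-effectiveness dates do not fit, and the utilisation comparators are loosely fixed

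*Protocol article*

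**What the plan says.** All references are to the protocol article.

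- **Evaluation of GLA:D® implementation, Table 2, Cost row:** "Health utilisation and sick leave/medication use survey at 3 months and 12 months post-programme (Patients"). Baseline is not listed.
- **Evaluation of effectiveness:** the registry will collect "all therapist- and patient-reported data from baseline, 3- and 12-months follow-up". The outcomes collected are said to be in Additional file 5, which is not shown.
- **Evaluation of cost-effectiveness:** "An exploration of healthcare utilisation pre- and post- participation in the GLA:D® programme will be conducted at each time-point", with a pointer to Additional file 3, and the result is to be "compared to national data from the TILDA study". Also: "A cost utility analysis will be conducted after 2 years of implementation", with the ICER taken one year after the intervention.
- **Abstract, Methods:** patient and cost outcomes are followed for up to 12 months after programme delivery.
- **Discussion:** "patient outcomes and cost effectiveness data collected after 1 year of implementation will be used" to make the case for funding to the Department of Health and the Health Service Executive. The Discussion also says that healthcare use is tracked by self-report.
- **GLA:D® pilot programme delivery:** entry requires "joint problems from knee and/or hip that have resulted in contact with the health care system".
- **Background:** TILDA data indicate that people with OA make more use of GP and outpatient services than people without it.

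**The concern.** A before-and-after comparison of utilisation needs a pre-programme value for every patient. Table 2 is the only place in the article that gives times for this survey by name, and it leaves that value out. A site working from the table could skip the baseline survey, and a contemporaneous baseline cannot be collected later.

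An ICER also needs costs and QALYs that cover the same period. If utilisation is timed from programme end and EQ-5D from baseline, the two windows do not match.

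The Discussion means these results to support a request for public funding. For that use three further things matter: when the result can exist, whether a fall in utilisation partly reflects how patients were selected, and whether the external comparator is a like population.

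**Working it through.** The article states no figure on this point that could be reproduced. The check is a comparison of sections, with some calendar arithmetic.

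**1. Baseline utilisation.** The Cost row gives 3 and 12 months and no baseline. The effectiveness section puts all patient-reported data on a baseline, 3- and 12-month schedule. The Discussion makes utilisation self-reported, so it falls under that general schedule. The cost-effectiveness section needs a value from before participation. Two sections therefore imply a baseline and the survey-specific row omits it.

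The pointer that should settle the matter fails. The cost-effectiveness section cites Additional file 3, which the design section identifies as the GRIPP-2 checklist; the list of collected outcomes is Additional file 5.

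**2. Time origin.** The Abstract and Table 2 count from programme end, and the ICER is set one year after the intervention. The effectiveness section speaks of 3- and 12-month follow-up without an origin. The Background gives a six-week exercise programme. Taking that as the time from baseline to programme end:

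- 12 months counted from programme end: 6 + 52 = 58 weeks from baseline.
- 12 months counted from baseline: 52 weeks.
- Possible gap: 58 − 52 = 6 weeks.

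**3. Calendar.** Suppose that the first patient starts on the first day of implementation.

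- Data cut at 1 year (52 weeks): a 12-month post-programme value needs 58 weeks, and 58 > 52, so no patient has one. Counted from baseline, only patients who enrolled at the very start would have one.
- Analysis at 2 years (104 weeks): 104 − 58 = 46, so patients who start in the first 46 weeks have a complete 12 months post-programme.

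The 2-year analysis date therefore fits a one-year patient horizon. The 1-year date in the Discussion does not, if it means a data cut.

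**4. Pre-period.** Entry is conditional on contact with the healthcare system. If the baseline survey's recall window includes that contact, pre-programme use is raised by selection, and some later fall would be expected without any programme effect. There is no comparison group to show how much. The recall window is not shown, so no size can be given.

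**5. TILDA.** The comparator is described only as national data. By the Background's own account use differs by OA status, so a comparison with all respondents would set patients with OA against a population that includes people with lower use.

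**The case against.** The strongest reply is that the general registry sentence already supplies the baseline. Table 2 describes proposed methods for implementation outcomes and is not an assessment schedule, and Additional file 5 may list utilisation at baseline. This stands in large part. A reader might infer from the Cost row that utilisation is collected only after the programme and that the cost increment cannot be computed. The documents do not support that. The defect is an incomplete row that conflicts with other sections.

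On the time origin, wherever the article states one for this project's patients it is the end of the programme. The phrase about change from baseline to follow-up names the two values subtracted, not when the clock starts. This also stands, so the 6-week gap is a possibility left open, not a stated mismatch. A reader might go further and infer that one-year totals are overstated by 6/52 = 11.5%. That would require the whole span from baseline to be treated as one year, which no section says.

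On the calendar, a reader might count three different horizons. There is one patient horizon, one year, in both the Abstract and the cost-effectiveness section; 2 years is when the analysis is run. The Discussion sentence is the outlier. It is worded as an expectation, and if it means data gathered from year 1 onward the conflict disappears.

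On the pre-period, eligibility sets no time window for the contact, entry routes include waiting lists and self-referral, and the comparison is called an exploration. The Discussion also concedes the limits of an uncontrolled pre-post design. All true, so the inflation is possible and not established. But the article defends the design by pointing to completed trials of exercise effectiveness, and that argument does not cover utilisation or cost.

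On TILDA, the wording does not say all respondents, and standardisation is a detail that an article may leave to an analysis plan. That is fair; what remains is that the comparator as named is open to a mismatched reading.

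**Conclusion.** The concern holds as a set of inconsistencies to reconcile and two cheap protections against bias. Three points are matters of text: the Cost row omits the baseline implied by the effectiveness and cost-effectiveness sections; the cost-effectiveness section points to the wrong additional file; and the Discussion's 1-year date does not fit the 2-year analysis if it means a data cut.

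The possible gap between cost and QALY windows is about 6 weeks. It assumes that the six-week exercise programme is the interval from baseline to programme end, and that one instrument is timed from baseline and the other from programme end. The finding that no patient has 12 months post-programme at 1 year rests on the same programme length and on reading the Discussion as a 1-year cut.

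The pre-period and TILDA points concern how the utilisation result would be read. Their size cannot be derived from the article.

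No stated number changes, and the article names implementation outcomes as primary. The changes are still worth making, because the cost result is intended for funders.

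**What to change.** 1. Add baseline to the Cost row of Table 2, and state one time origin for both the utilisation survey and EQ-5D.
2. Align the Discussion with the cost-utility analysis after 2 years, restricted to patients whose 12-month window has closed.
3. Correct the reference to Additional file 3 in the cost-effectiveness section so that it points to the file listing the collected outcomes.
4. Add a sensitivity analysis that excludes the qualifying referral contact from the pre-programme period.
5. Specify the external comparator as TILDA respondents with OA, standardised by age and sex.

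The cost is wording, one added analysis and a narrower comparator. If baseline utilisation is not already collected, it also means one more completion of an existing survey at enrolment. The result for advocacy would come later than the Discussion suggests.

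### Table 2 assigns feasibility only a provider survey taken at training, before any pilot session, so the result will show anticipated feasibility; secondarily, fidelity rests on self-report that yields no degree

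*Protocol article*

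**What the plan says.** The section on evaluation of GLA:D® implementation states that "acceptability, adoption, appropriateness, cost, feasibility, fidelity, penetration and sustainability will be evaluated as outlined in Table 2", so the table fixes how each outcome is measured.

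- **Feasibility** is defined as "The extent to which the programme can be successfully used or carried out within a given setting". The only listed source is: "Collected with a survey at training course with strategies to overcome specific feasibility barriers discussed (Providers").
- **Fidelity** is defined as the degree to which delivery follows the original protocol. The only listed source is a provider interview, which asks "Did you make specific changes to the original programme" and then what was changed.

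The same section says that implementation outcomes will be summarised by frequencies and proportions, or by means or medians. It plans thematic analysis for the interviews. Those interviews cover 8–10 physiotherapists who delivered the pilot within five months and "those who have not implemented the programme, if appropriate". Patients are sampled for interview partly on "disability level, duration of symptoms and number of attended sessions".

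The section on training of physiotherapists describes an engaged convenience sample invited "to take part in the first GLA:D® training course and pilot study". The course gives them an "online platform with all the material needed to deliver GLA:D® locally in the clinic".

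**The concern.** Feasibility concerns whether the programme can be run successfully in a given clinic. A survey taken at the course, while ways round the barriers are being discussed, can record only what trainees anticipate. Problems that appear once classes start, such as lack of space, staff time or referrals, cannot enter that result unless they were foreseen.

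Fidelity is a lesser problem. The question is relevant and is put after delivery, but it is answered by the people whose delivery is being judged. The answers are open text, which does not readily give a degree or a proportion.

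The Discussion calls the implementation outcomes primary. Stage 3 uses the pilot results to adapt the strategies before the national launch. If feasibility is reported as Table 2 sets out, the steering committee would have a feasibility result that contains no experience of delivery.

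**Working it through.** The plan states no figure on this point, so the check compares definitions, sources and timing.

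**1. Order of events.** Under training of physiotherapists, the pilot providers attend the course and receive the materials for use in their clinics. Under pilot programme delivery, the trained physiotherapists then invite patients and run the sessions. A survey at the course therefore precedes the first pilot session.

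**2. Sources after training, by Table 2 row.**

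| Outcome | Source after training |
|---|---|
| Acceptability | Satisfaction surveys at 3 and 12 months; interviews |
| Adoption | Registry, including sites trained against sites implementing |
| Appropriateness | Satisfaction survey at 3 months; interviews |
| Cost | Utilisation survey at 3 and 12 months; cost-effectiveness analysis; interviews |
| Feasibility | None listed |
| Fidelity | Provider interview only |
| Penetration | Registry counts of those screened and participating |
| Sustainability | Sites still running at 12 months and at project end; patient activity at 3 and 12 months; interviews |

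Feasibility is the only one of the eight rows with no source after training.

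**3. Related data elsewhere.** Three items bear on feasibility after delivery: the provider and patient interviews on barriers and enablers, the adoption count of sites trained against implementing, and the appropriateness question on compatibility with the setting. None is assigned to the feasibility row.

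**4. Fidelity against the planned summary.** The programme has countable parts: two to three education sessions and 12 exercise sessions, which is 2 + 12 = 14 to 3 + 12 = 15 sessions per programme. Sessions delivered out of this number would give a degree. The listed question instead gives a yes or no with a free description. If the yes or no were tabulated over 8–10 providers, each provider would move the proportion by 1/10 = 10 to 1/8 = 12.5 percentage points, and the figure would say nothing about how large the departure was.

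**5. Attendance.** Sampling patients on sessions attended implies that attendance will be known. It chiefly reflects patient adherence, however, so it does not replace a count of sessions delivered.

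**The case against.** The best defence is that the plan as a whole gathers more than these two rows suggest. Providers are interviewed after the pilot about barriers to delivery. A site that trained and never ran a class would appear under adoption as not implementing. Stage 3 draws on all quantitative and qualitative pilot results and on each strategy's own method of evaluation, with yearly review. The definition speaks of what can be carried out, and a survey of barriers in the provider's own setting partly answers that. The table describes its methods as proposed, and the interview guide (Additional file 4) and registry outcomes (Additional file 5) are not shown.

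Much of this stands, and it rules out several stronger readings that a reader might infer:

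- *Nothing in the plan measures feasibility after delivery.* The documents do not support this. Relevant data are collected; they are not assigned to this outcome.
- *A site that never ran a class could still be scored as feasible.* The plan describes no feasibility score, and the adoption row would show such a site.
- *Fidelity does not measure what is defined.* Asking deliverers what they changed from the original programme does address the construct. The weakness is unverified self-report without a degree.
- *No objective fidelity figure will exist.* This cannot be known without the additional files.
- *Both measures are biased towards success.* The engaged convenience sample makes optimistic expectations plausible, but the survey asks about barriers and the interview about changes, so the direction is not established.
- *Non-implementers are left out.* They are named, and 8–10 interviews from 8–10 trained physiotherapists could reach nearly all of them. The qualifier may only allow for there being none, but no criterion is given.

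The defence does not remove the mismatch in the feasibility row. The text says that outcomes are evaluated as the table sets out, and the table gives this outcome only a source that precedes delivery.

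**Conclusion.** The point holds for feasibility: followed as written, the result would describe anticipated feasibility among engaged trainees and would not show how far the programme was carried out in the setting. For fidelity it holds in a weaker form: the source fits the construct but is unverified and does not readily yield the degree or the proportions planned.

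The size is one mismatched outcome and one weakly measured outcome out of eight, in a project where implementation outcomes are primary. The effect on Stage 3 is limited, because the related interview and adoption data also reach the steering committee. This is a cheap improvement worth making and does not invalidate the pilot.

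The conclusion assumes that the training-course survey is not repeated and that the additional files add no source for these two rows. If they do, Table 2 still needs to point to it.

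**What to change.** 1. Repeat the training-course feasibility survey with all trained physiotherapists at about the five-month point, whether or not they implemented. Use this as the feasibility result, with the training survey as its baseline.
2. In the feasibility row, also cite the sites trained against sites implementing and the post-delivery interview data on barriers, both already planned.
3. Report fidelity also as sessions delivered against the programme as the protocol describes it (two to three education and 12 exercise sessions). Report sessions attended per patient separately, as adherence, and keep the interview to explain departures.
4. Invite every trained physiotherapist who did not implement to interview, in place of the open qualifier.

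The cost is one extra short survey for 8–10 people, the corresponding edits to Table 2, and a simple record of sessions delivered if the registry does not already hold one. The respondent burden is small, and neither treatment nor patient eligibility changes.
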